#### Secondary outcome measures

The Fear Avoidance Belief Questionnaire (FABQ) is a secondary "participation" outcome measure in our study. It focuses specifically on a subject's belief about how physical activity and work affects low back pain [46]. Fritz et al [47] determined that screening for fear-avoidance beliefs may be useful for identifying subjects at risk of prolonged disability and work absence.

Secondary "activity" outcome measures include the 24-hour Physical Activity Scale (PAS) and the 5-minute walk test. The PAS is a survey that requires the subjects to estimate the amount of time spent at different types and levels of physical activity during a typical day [48]. Its purpose is to monitor the level of activity in the subjects enrolled in the study, both as an outcome measure as well as an activity-monitoring strategy for all subjects. The 5-minute walk test will measure how far each subject can walk in a 5-minute period. The speed is self-selected by the subject. Excellent test-retest reliability (ICC = 0.99) has been established for this measure [42].

Secondary "physical" outcome measures include the following tests: lower quarter neurological screen, straight leg raising (SLR), lower quarter flexibility, lumbar spine range of motion, and lumbar spine instability. The purpose of the lower quarter neurological screen is to assess sensation, strength, and deep tendon reflexes (DTRs) before and after the intervention. The screen was derived from several different sources. The sensory testing points were derived and modified from the American Spinal Injury Association (ASIA) screen [49,50]. Sensation to pin prick (sharp/dull discrimination), light touch, and vibration (using a 256-Hz tuning fork) will be assessed. The muscles chosen for manual muscle testing were also derived from the ASIA screen. The muscle testing procedure was derived from Kendall et al [50]. Gastrocnemius/Soleus (S1) manual muscle test grading was based on the work of Lunsford and Perry [51]. Patellar and Achilles DTRs were assessed.

The Passive Straight Leg Raise Test (PSLR) will be used to assess the mechanical movement of the nerves in the lower extremity and to assess symptoms [52,53]. The PSLR will be quantified using a goniometer to measure hip flexion ROM, and a pain VAS to quantify pain complaint. In addition, a crossed straight leg raise (CSLR) sign, in which elevation of the leg produces symptoms on the contralateral spine and/or leg [54], will also be noted. The PSLR test has been shown to have high sensitivity (i.e., a negative PSLR is highly indicative of no presence of a herniated lumbar disc) and low specificity (i.e., a positive test is not highly indicative of the presence of a herniated disc). On the other hand the CSLR sign has been show to have a low sensitivity (0.29) and high specificity (0.88) [54]. A positive PSLR will be considered one in which a patient's symptoms are reproduced by ankle dorsiflexion.

Lower quarter flexibility/muscle length measurements will be assessed to determine the effect of the intervention on muscle flexibility, and will be derived from the amount of movement attained at the relevant joint for each muscle group. Lumbar spine range of motion (ROM) will be used to quantify lumbar spine mobility during forward flexion, extension, and right and left lateral flexion for each subject. Due to post-surgical restrictions, lumbar ROM will only be measured immediately following the intervention and one year after surgery. Post-surgical restrictions are in place to prevent the patient's mobility from compromising the surgery. Lumbar spine ROM in the sagittal plane will be assessed using a double inclinometer method, which has been proven to be a highly reliable and valid measurement technique [55]. Lumbar spine ROM in the frontal plane will be assessed using a tape measure.

Lumbar spine instability will be tested to gain information on the nature of the subject's symptoms. With the subject's torso prone on a treatment table and both lower extremities on the floor, the examiner will apply posterior-to-anterior (P-A) pressure at each lumbar spinous process to the end of the perceived range of motion. Reproduction of pain, and the involved segment, will be noted. If the subject reports a full reduction of symptoms at the painful segment when lifting the LEs, it will be considered a positive test for instability of that segment. The prone instability test has been shown to be more reliable than the segmental instability test [56].

### Follow-up period

All of the previously described questionnaires will be administered during face-to-face evaluation sessions occurring four to six weeks after surgery, at the end of the intervention period, and one year after the surgery. They will be administered via the regular mail during the follow-up period (every six months thereafter for the next four years). The mailings will be preceded by phone calls from the study coordinators during which the subjects will be asked questions regarding their symptoms and activity level. If the subjects report that they are symptomatic, then the following questionnaires will be sent: OD, RM, SF-36^®^, SQOL, FABQ, and PAS. In this case, subjects will also receive the pain VAS forms for sitting and walking, and will be asked to report their typical symptoms (intensity and location) during these activities, but they will not need to mark the pain VAS forms immediately after sitting or walking for a certain time. If, however, the subjects report that they are asymptomatic at the time of the follow-up call, only the PAS will be sent.

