The study is divided into three phases, a protocol development phase, an implementation or intervention phase, and a follow-up phase. During the protocol development phase, a team of physical therapist researchers and clinicians developed, tested, and standardized the post-surgical intervention and testing protocols. During the intervention phase, a two-group, pretest-posttest design will be used, with participants being randomly assigned to one of two groups: one session of back care education, or a back care education session followed by the 12-week USC Spine Exercise Program. This design will allow for the analysis of the effects of treatment over time. The outcome measures in the study (see below) will be assessed before and after the post-surgical intervention period. The evaluators, as well as the data managers, will be blinded to group allocation. After the end of the intervention phase, follow-up assessments of selected outcome measures will be conducted on all participants every six months, beginning one year and ending five years after the date of surgery (the follow-up phase). The follow-up phase will allow for the analysis of the stability of the effect of treatment over time.

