### Study sample

One hundred individuals between the ages of 18 and 60 who consent to undergo lumbar microdiscectomy will be recruited to participate in this study. Potential subjects will be medically screened, pre- and post-surgically, by one of 27 surgeons who have been informed about the study. Patients deemed eligible for the study based on the medical screening, will be offered the opportunity by the surgeon's nurse coordinator to consult with a study coordinator regarding participation in the study. The nurse coordinator will complete an eligibility screening form on each individual screened for the study, and the study coordinator will track the number of potential participants screened and the reasons for exclusion from the study.

If the potential participant agrees to meet the responsibilities of the study, an enrollment appointment will be scheduled with a "blinded" evaluator. The evaluator will review the informed consent, and a summary of the Health Insurance Portability and Accountability Act of 1996 (HIPAA) policy, in detail with prospective participants. The purpose of the study, the procedures to be employed, any potential risks and benefits of participation, random placement into one of two groups, and the responsibilities of the participants and the members of the research team, will be discussed with the potential participants. All questions regarding the study will be answered fully. When the individual signs the consent form, the evaluator will initiate testing of the outcome measures. Successful completion of the evaluation will be reported to the study coordinator, who will inform the study participant about his or her group allocation. The study participant will choose one of the 17 participating clinics as the site of care delivery.

There will be no enrollment restrictions based on gender, race, or ethnic origin. There is no reason to expect that this study population will not reflect an adequate racial cross-section of Los Angeles and surrounding communities.

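### The calls at months 18 to 60 that decide whether primary questionnaires are mailed are made by study coordinators, the role that knows allocation and that the stated blinding does not cover

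*Protocol article*

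**What the plan says.** Four statements in the protocol article bear on this point.

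- **Who knows allocation.** Study sample: "Successful completion of the evaluation will be reported to the study coordinator, who will inform the study participant about his or her group allocation".
- **Who is blinded.** Methods/design: "The evaluators, as well as the data managers, will be blinded to group allocation". The Abstract names the same two roles. Methods/design also has the blinded evaluators carry out the face-to-face measurements, and under Follow-up period the last of those sessions is one year after surgery.
- **Who calls afterwards.** Follow-up period, on the six-monthly mailings that run to five years after surgery: "The mailings will be preceded by phone calls from the study coordinators during which the subjects will be asked questions regarding their symptoms and activity".
- **What the call decides.** "If the subjects report that they are symptomatic, then the following questionnaires will be sent": the Oswestry (OD), Roland-Morris (RM), SF-36, SQOL, FABQ and PAS, together with pain VAS forms. Otherwise: "If, however, the subjects report that they are asymptomatic at the time of the follow-up call, only the PAS will be sent".

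**The concern.** The long-term comparison is a stated purpose of the trial, and Methods/design assigns to the follow-up phase the question of whether the treatment effect lasts. In that phase the only live contact described is a telephone call about symptoms, made by a role that knows the participant's group. The call also determines whether the OD, RM, SF-36, SQOL and pain VAS are collected at all at that time point.

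The article gives no definition of symptomatic and mentions no script. After disc surgery many people will have mild or intermittent symptoms, and their answer can depend on how the question is put and followed up. If the caller's knowledge of the arm affects this, the two arms will differ in who supplies primary data, for a reason unrelated to treatment. At stake is whether the late questionnaire and pain data are collected comparably in both arms.

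**Working it through.** The article gives no figure for this point, so the check is a comparison of statements followed by a count of what is exposed.

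**Roles set side by side**

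| Role | Knows or discloses allocation | Stated as blinded | Contact at months 18 to 60 |
|---|---|---|---|
| Evaluators | No | Yes | None described |
| Data managers | No | Yes | None described |
| Study coordinators | Yes (Study sample) | No | Make the symptom call (Follow-up period) |

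The caller's role is therefore named, and it is the role named as disclosing allocation. The article does not say that the callers are blinded or that they are different people from those who disclose allocation.

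**Contacts affected**

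- Schedule: every six months after the one-year visit, for four years, which gives months 18, 24, 30, 36, 42, 48, 54 and 60. That is 4 × 2 = 8 contacts.
- Maximum number of calls: 8 × 100 participants = 800.
- If the 30% attrition in the Sample size section applied at every wave: 8 × 70 = 560.

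**Outcomes affected.** The primary measures collected after one year are the OD, RM, SF-36, SQOL and pain VAS, and all of them depend on the call. So does the FABQ, a secondary measure. The PAS goes to everyone. The 50-foot walk, sit-to-stand and modified Sorensen tests end at one year and are not affected.

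**What a shift would mean (assumed, not from the document).** Take 50 × 0.7 = 35 retained per arm, and suppose the caller's knowledge lowers the share reporting symptoms in one arm by s. The primary sets lost in that arm are 35 × s per wave, and eight times that over the phase, out of 35 × 8 = 280 possible.

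| Assumed s | Lost per wave | Lost over 8 waves |
|---|---|---|
| 5 points | 35 × 0.05 = 1.75 | 14 |
| 10 points | 35 × 0.10 = 3.5 | 28 |
| 15 points | 35 × 0.15 = 5.25 | 42 |

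**Direction.** Suppose more mildly affected exercise participants come to report no symptoms. Under the mailing rule they return no OD, RM, SF-36 or SQOL, so the scores left in that arm are the worse ones, and exercise looks worse on the observed data. If unsent forms were instead scored as no disability, exercise would look better. The article states no handling of unsent forms, so the direction is open.

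**The case against.** The strongest reply has five parts.

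1. *The coordinator classifies nobody.* This stands. A reader might infer that the coordinator judges who is symptomatic, but the text makes it the participant's own report. What remains is influence through phrasing, prompting and interpretation of the answer.
2. *No blinding claim is broken.* This stands. A reader might see a contradiction, but blinding is claimed only for evaluators and data managers, and that claim can remain true throughout.
3. *The call is not an outcome.* This stands in part. Symptom status by telephone is not a listed outcome, and the Data analysis section plans no comparison of the proportion with symptoms. A reader might infer a false lasting benefit of exercise; the documents do not support that, for the reason given under direction above. But the call still decides whether listed primary outcomes are collected.
4. *Participants know their group and complete the late forms themselves, so blinding the caller gains little.* The first half is true, and that source of bias would remain. The caller's influence is an additional source and can be avoided.
5. *An article condenses: a script, a definition and a separation of staff may exist elsewhere.* This is fair for the script and the definition, and separate coordinators are neither stated nor excluded: the article refers to one coordinator when allocation is disclosed and to several for the calls. It does not remove the point, because the article itself assigns both tasks to the same named role. If the callers are in fact kept unaware of allocation, one sentence would settle it.

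**Conclusion.** The concern holds as a gap in the scope of blinding. At all eight contacts from 18 months to 5 years, a role that knows allocation conducts the call on which collection of the late primary questionnaires and pain scales depends. Collection can therefore differ by arm for a reason unrelated to treatment.

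The conclusion rests on two readings: that the coordinators who call know allocation, as the role description implies, and that a symptom question without a stated standard leaves room for influence. The extent is up to 800 calls, or about 560 with 30% attrition throughout. The shifts of 5 to 15 points are illustrations only; nothing in the document shows that a shift of any size would occur or which arm it would favour.

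Sending the primary forms only to participants with symptoms is a separate and larger problem, which blinding the caller would not cure.

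**What to change.** - Have the calls at months 18 to 60 made by existing staff without access to allocation, for example the blinded evaluators.
- Use a fixed script with one standard symptom question, opening with a request not to disclose group.
- Extend the blinding statement in Methods/design to these calls. If the callers are already kept unaware of allocation, say so there.

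**Cost.** Up to 800 short calls (about 560 with 30% attrition throughout) move between existing staff, and a script has to be written. No visits, participants or measurements are added. If evaluators call, a participant who reveals the group cannot affect his or her own face-to-face assessments, which end at one year, though later calls to that participant would no longer be blinded.

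**What it leaves.** Participants still know their arm when they answer, and the rule on who is sent the primary forms needs its own correction.

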## Background

Approximately 12–33% of the adult work force is affected by low back pain each year, and it has been suggested that between 70% and 95% of adults will suffer from low back pain at some time during their lifetime [1-5]. Unlike other orthopedic disorders, the expenses associated with management of back pain have increased over the last 20 to 30 years [1,2]. A recent study on health care expenditures for people with back pain in the United States reported that total expenditures were over $90 billion in 1998, and that these individuals incurred 60% higher expenditures than those without back pain [6]. Despite continuous clinical and scientific efforts, low back pain remains an ever-present, quality-of-life-related, health problem.

The lumbar intervertebral disc is susceptible to injury and early degeneration, which often result in pain and disability. To effectively remedy these problems, treatment of symptomatic lumbar disc herniations has continuously evolved. Surgeons have sought to reduce operative trauma to the spine by adopting minimally invasive techniques such as microdiscectomy, (microscope-assisted or endoscopic), which is used to treat single-level disc injury in working-age adults. Despite widespread use of this technique, there are few reports of long-term results [7-10]. Early success rates ranging from 70–91% have been reported [7,11-14]. Limited available data related to long-term follow-up demonstrates that the success rate decreases to 60–70% after three to ten years [8]. However, these success rates may be influenced by post-operative care.

The current practice pattern for management of activity post-operatively has three distinct directions. A common, but not studied, approach includes 4 to 16 weeks of limited activity following the surgery. A second approach, advocated more recently by Carragee et al [15], suggests that eliminating post-operative activity restriction leads to enhanced short-term outcomes for patients after limited open discectomy. A third approach incorporates an early strengthening intervention into the post-surgical regimen [16-19].

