### Outcome measures

We have used the International Classification of Functioning (ICF) conceptual framework [31,32] to classify the study's outcome measures (Figure 6). The ICF framework categories (body functions and structures, activity, participation) correspond, respectively, to Nagi's disablement model [32,33] categories (impairments, functional limitation, disability). We divided the outcome measures into primary and secondary variables. The primary outcome measures will provide an assessment of the intervention and the secondary outcome measures are descriptive, informing, and hypothesis-building. Testing of all outcome measures will be administered at the post-surgical/pre-intervention assessment, post-intervention assessment, and 1-year post-surgical assessment. In addition, completion of questionnaires and pain visual analog scales (VASs) will occur every six months after the 1-year post-surgical assessment, for the remaining four years of the study.

The subject must complete all sections of each questionnaire for the questionnaire to be considered valid. Research personnel will ensure that all sections are completed during each assessment. Incomplete questionnaires will not be accepted for data entry.

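### From 18 months to 5 years, the questionnaire and pain primary outcomes are collected only from participants who report symptoms, so the late comparison of these outcomes is not a randomised one

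*Protocol article*

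**What the plan says.** The Follow-up period section has all questionnaires completed face to face at four to six weeks, at the end of the intervention and at one year. It then says in general terms that they will be mailed "every six months thereafter for the next four years". A call from the study coordinators comes before each mailing and sets its content:

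- Symptomatic: "If the subjects report that they are symptomatic, then the following questionnaires will be sent: OD, RM, SF-36", followed in the list by the SQOL, FABQ and PAS. The pain scales are tied to the same condition: "In this case, subjects will also receive the pain VAS forms for sitting and walking".
- Asymptomatic: "If, however, the subjects report that they are asymptomatic at the time of the follow-up call, only the PAS will be sent".

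Two other sections describe the same period differently. Outcome measures states that "completion of questionnaires and pain visual analog scales (VASs) will occur every six months after the 1-year post-surgical assessment", with no symptom condition. Methods/design states that "follow-up assessments of selected outcome measures will be conducted on all participants every six months".

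The Oswestry, Roland-Morris, SF-36, SQOL and pain VASs are listed as primary outcomes. The FABQ and PAS are secondary. Data analysis tests primary and secondary outcomes for immediate and long-term effects by two-factor MANOVA with repeated measures for time. No section assigns a score to a participant who was not sent the forms.

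**The concern.** Whether a participant has symptoms at 18 months or later is a consequence of what happened after randomisation, and the stated hypothesis is that exercise lowers pain and disability. If that is right, fewer exercise than control participants will pass the symptom filter, and those who pass will be the ones who did poorly in each arm. Randomisation no longer makes the two groups comparable. The data that would show the benefit, good scores in people who recovered, are the data not collected.

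What is at stake is the period from 18 months to five years, which the Background section presents as part of the trial's purpose. A secondary risk concerns the call itself. It is made by study coordinators, and Study sample describes "the study coordinator, who will inform the study participant about his or her group allocation". The caller may therefore know the arm and could influence how symptoms are reported.

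**Working it through.** **1. How many assessments are affected.** The last unconditional assessment is at 12 months and follow-up ends at 60 months. (60 − 12)/6 = 8 mailings: months 18, 24, 30, 36, 42, 48, 54 and 60.

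**2. Do the sections agree?** Outcome measures (questionnaires and VASs every six months) and Follow-up period (only if symptomatic) cannot both be followed. Follow-up period also conflicts with its own general statement that the questionnaires will be mailed. Methods/design promises only selected measures on all participants. Since the PAS and the call reach everyone, that sentence can be read consistently with the filter, but it sits poorly with it.

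**3. The plan's own sample size.** Sample size gives about 50 per group, 30% attrition, alpha 0.05 and power 0.8. It gives no SD, named outcome or scale for its 50% difference, so 50 cannot be reproduced, nor is it shown to be wrong. Back-solving: 50 × 0.7 = 35 evaluable per arm. With two-sided 0.05 (sidedness assumed) and 80% power, the normal approximation gives (1.96 + 0.84) × √(2/35) = 0.67 SD; the t-test gives 0.68 SD. I use 0.68.

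**4. One model for the filter.** Higher scores are worse. Control scores are N(0, 1) and exercise scores N(−0.68, 1). A latent symptom severity is shifted by the same amounts and has correlation r with the score within each arm. A participant is symptomatic when severity exceeds a cut-off c, set so that a share p of controls is symptomatic. With arm mean μ, a = c − μ and λ = φ(a)/(1 − Φ(a)):

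- share symptomatic = 1 − Φ(a)
- mean score among symptomatic = μ + rλ
- variance among symptomatic = 1 − r²λ(λ − a)

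Lowest case (p = 0.30, r = 1): c = 0.524. Control λ = 1.159, so the mean is 1.159. Exercise a = 1.204, share 0.114, λ = 1.691, so the mean is −0.68 + 1.691 = 1.011. Difference 1.159 − 1.011 = 0.148 SD. Numbers: 35 × 0.30 = 10.5 and 35 × 0.114 = 4.0. SE = √(0.514²/10.5 + 0.420²/4.0) = 0.263. Power is 8% (noncentral t).

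Highest case (p = 0.70, r = 0.5): c = −0.524. Control mean 0.5 × 0.497 = 0.249. Exercise share 0.438, mean −0.68 + 0.5 × 0.900 = −0.230. Difference 0.479 SD. Numbers 24.5 and 15.3. SE = √(0.934²/24.5 + 0.913²/15.3) = 0.300. Power is 34%.

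| Controls symptomatic | r | Supplying data (control / exercise) | Observed difference | Share of 0.68 kept | Power |
|---|---|---|---|---|---|
| 30% | 1.0 | 10.5 / 4.0 | 0.15 SD | 22% | 8% |
| 70% | 1.0 | 24.5 / 15.3 | 0.28 SD | 41% | 26% |
| 30% | 0.5 | 10.5 / 4.0 | 0.41 SD | 61% | 11% |
| 70% | 0.5 | 24.5 / 15.3 | 0.48 SD | 70% | 34% |

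With all 35 per arm measured, power is 80% and the 0.68 SD is estimated without this selection.

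**5. The sign can change.** Invented scores, 35 per arm. Control: 14 at 0, 11 at 10, 10 at 40. Exercise moves the 11 mild cases to 0 and changes nobody else. Everyone measured: (110 + 400)/35 = 14.6 against 400/35 = 11.4, so exercise is better. Symptomatic only: 510/21 = 24.3 against 400/10 = 40.0, so exercise looks worse although no one was harmed.

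**6. Repeated measures.** A standard repeated-measures MANOVA uses only participants with every time point. Were symptom status independent across mailings, those complete at all eight would number 35 × 0.7⁸ = 2.0 per arm at a 70% share and practically none at 30%. Real symptoms persist, so there would be more, but they would be the persistently symptomatic.

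**The case against.** The article does not say that the analysis is restricted to symptomatic participants. A separate analysis plan might assign scores to those who report no symptoms. That is conceivable for the pain scales and perhaps for Oswestry and Roland-Morris. It is weak for the SF-36, SQOL and FABQ, because answering one call as asymptomatic does not fix quality of life or fear-avoidance beliefs. The rule is about data collection, and analysis cannot restore forms that were never sent.

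The filter also spares well participants some burden. That stands, but they already receive the PAS by post.

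Some stronger readings are tempting and should not be drawn:

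- *Staff who know the allocation decide who supplies data.* The trigger is the participant's own report, and no coordinator judgement is described. The text does not say that the caller is the person who disclosed the allocation. Participants know their arm, so a blinded caller would not remove reporting bias.
- *Methods/design promises the questionnaires to everyone.* It promises selected measures only. The clear conflict is between Outcome measures and Follow-up period.
- *The whole long-term comparison is lost.* The one-year visit is face to face and unconditional.
- *A benefit is always hidden, by about three quarters.* Roughly that loss appears only when symptoms are a perfect cut-off of the score and few controls are symptomatic. Step 5 shows that the direction is not fixed.

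**Conclusion.** The point holds for the Oswestry, Roland-Morris, SF-36, SQOL, FABQ and pain VASs at the eight mailings from 18 months to five years. Followed as written, the late comparison of these outcomes is conditioned on a post-randomisation variable that the intervention is meant to change. The PAS, and all comparisons up to and including one year, are unaffected. The unblinded caller is a secondary risk.

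On the assumptions in the working, about 10–25 controls and 4–15 exercise participants would supply data, the observed difference would be 0.15–0.48 SD (22–70% of the true effect), and power would be about 8–34%. These figures are an illustration. The effect in SD units, the symptomatic share and the correlation are not in the document. The nearest figure is the Background statement that "the success rate decreases to 60–70% after three to ten years", and success there is not defined as freedom from symptoms, hence the wide range. Sample size also lists elimination of symptoms as a reason for attrition, so taking 30% attrition and then the symptomatic share may count some people twice. The selection problem itself does not depend on any of these numbers.

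**What to change.** Mail the same full packet (Oswestry, Roland-Morris, SF-36, SQOL, FABQ, PAS and pain VASs) to every randomised participant at every six-month follow-up, whatever is said on the call. Keep the call as a reminder and record the reported symptom status as a separate variable. Reword Follow-up period, Outcome measures and Methods/design so that they state the same rule.

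The cost is protocol wording, extra postage and modest extra time for participants who are well. No extra patients or visits are needed. The change has to be in place before the 18-month mailings, because forms not sent cannot be completed retrospectively.
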